## Abstract

**Background:**

The TRIAL-STIM Study aims to assess the diagnostic performance, clinical outcomes and cost-effectiveness of a screening trial prior to full implantation of a spinal cord stimulation (SCS) device.

**Methods/design:**

The TRIAL-STIM Study is a superiority, parallel-group, three-centre, randomised controlled trial in patients with chronic neuropathic pain with a nested qualitative study and economic evaluation. The study will take place in three UK centres: South Tees Hospitals NHS Foundation Trust (The James Cook University Hospital); Basildon and Thurrock University Hospitals NHS Foundation Trust; and Leeds Teaching Hospitals NHS Trust. A total of 100 adults undergoing SCS implantation for the treatment of neuropathy will be included. Subjects will be recruited from the outpatient clinics of the three participating sites and randomised to undergo a screening trial prior to SCS implant or an implantation-only strategy in a 1:1 ratio. Allocation will be stratified by centre and minimised on patient age (≥ 65 or < 65 years), gender, presence of failed back surgery syndrome (or not) and use of high frequency (HF10™) (or not). The primary outcome measure is the numerical rating scale (NRS) at 6 months compared between the screening trial and implantation strategy and the implantation-only strategy. Secondary outcome measures will include diagnostic accuracy, the proportion of patients achieving at least 50% and 30% pain relief at 6 months as measured on the NRS, health-related quality-of-life (EQ-5D), function (Oswestry Disability Index), patient satisfaction (Patients’ Global Impression of Change) and complication rates. A nested qualitative study will be carried out in parallel for a total of 30 of the patients recruited in each centre (10 at each centre) to explore their views of the screening trial, implantation and overall use of the SCS device. The economic evaluation will take the form of a cost–utility analysis.

**Discussion:**

The TRIAL-STIM Study is a randomised controlled trial with a nested qualitative study and economic evaluation aiming to determine the clinical utility of screening trials of SCS as well as their cost-effectiveness. The nested qualitative study will seek to explore the patient’s view of the screening trials, implantation and overall use of SCS.

**Trial registration:**

ISRCTN, ISRCTN60778781. Registered on 15 August 2017.

**Electronic supplementary material:**

The online version of this article (10.1186/s13063-018-2993-9) contains supplementary material, which is available to authorized users.

## Background

Approximately 20% of the adult European population has significant chronic pain, and 7–8% of the population has chronic pain with neuropathic features [1–3]. Health-related quality of life is significantly poorer in people with chronic pain than in those without [4], and poorer in people with neuropathic pain than in those with non-neuropathic pain [5]. In routine clinical care, up to 50% of patients with neuropathic pain fail to obtain pain relief from analgesic medicines [6].

In 2008, the National Institute for Health and Care Excellence (NICE) recommended spinal cord stimulation (SCS) as an effective and cost-effective treatment for severe neuropathic pain refractory to medical management conditional on a screening trial being conducted before a final implant of SCS in every case [4, 7]. The evidence for effectiveness and cost-effectiveness of such SCS screening trials still remains unclear.

### SCS screening trial and purpose

An SCS screening trial consists of the insertion of a wire (lead) introduced into the epidural space of the spinal cord through a needle puncture. The lead is then positioned to target the pain by passing current into the lead from an external power source, generating paraesthesia over the painful area. Pain coverage is expressed as a percentage of the whole area of pain covered by the paraesthesia. In patients where it is possible to achieve ≥ 80% coverage, the wire can be fixed to the spinal fascia through an open procedure and tunnelled to exit through the skin away from the incision. This technique is known as a definitive trial because the same wire is used later to attach to a battery if the trial is successful [8]. In some cases the implantation of the lead may be guided by anatomical landmarks rather than patient feedback. In an alternative technique known as a temporary trial, a wire is simply fixed to the skin at the site of the epidural needle puncture of the back by sutures or tape. The wire can be removed without the need for a surgical intervention at the end of the trial but requires a repeat implantation in the case of a successful trial. Trials can last from a few minutes (‘on-table trial’) to a few weeks (‘home trial’).

The screening trial period allows the patient to test the efficacy of SCS therapy directly and specifically. An expert panel defined a successful trial as the patient reporting ≥ 50% pain relief during the trial with stable or reduced pain medications, with at least stable levels of daily activity [9].

### Evidence for SCS screening trials as a predictor of long-term success

SCS screening trials are recommended by consensus expert opinion and national guidance in many countries, including the United Kingdom. However, the research literature to date has not provided definitive evidence to support the value of screening trials for SCS and in particular their ability to reliably predict the long-term success of SCS therapy.

The PROCESS RCT trial randomised neuropathic pain of failed back surgery syndrome (FBSS) compared SCS to conventional medical management; 95% of the patients receiving SCS reported ≥ 50% pain relief at the screening trial phase, but by contrast only 48% reported the same outcome at 6-month follow-up [10]. Another RCT compared SCS to reoperation in FBSS; 19/24 (80%) subjects reported a successful screening trial, but only 9/15 (60%) continued to report ≥ 50% pain relief at the 2-year follow-up [11]. However, no pain outcome data were available for patients who failed the trial.

Similarly, the SENZA randomised trial comparing high-frequency SCS to conventional SCS reported that 90/97 (92.8%) of subjects who trialled a higher frequency of SCS and 81/92 (88.0%) subjects who were trialled with traditional SCS were eligible for implantation [12]. By 12 months the figures for ≥ 50% pain relief dropped to 78.7% and 51.3% respectively. Oakley et al. [13] showed that 55% (18/33) of patients had ≥ 50% pain relief at the 6-month follow-up compared to 75% in the trial period. Screening trials have been shown to exclude good candidates for SCS. Twelve patients who failed to obtain ≥ 50% pain relief during an SCS screening trial still received an implanted SCS device [13]. At follow-up, a third of the patients reported pain relief rates of 44–88%. The authors concluded that the screening trial is not the sole predictor of long-term success but, again, did not assess pain outcomes in trial failures.

A retrospective study compared a 15-min on-table trial to a 5-day home trial and found a 98% (53/54) success rate for 15-min trials compared to 90% (47/52) for 5-day home trials [14]. The authors concluded that since both methods appeared to have equivalent predictive value for successful long-term outcomes, home trials should be eliminated based on increased therapeutic failures, greater risk of infection and additional therapy costs.

### Hypothesis and aims

We hypothesise that a no-SCS screening trial strategy will be superior to an SCS screening trial and more cost-effective. Specific aims of this study are to:compare the patient-related outcomes of an SCS screening trial strategy to a no-trial implantation-only strategy;determine the diagnostic performance (e.g. sensitivity and specificity) of an SCS screening trial;compare the cost-effectiveness of a screening trial strategy to a no-test implant-only strategy; andassess the expectations and experiences of patients for the use of an SCS screening trial.

## Methods and design

### Study design

The study is designed as a superiority, parallel-group, three-centre RCT in patients with chronic neuropathic pain with a nested qualitative study and economic evaluation. Participants will be allocated in a 1:1 ratio to either a strategy of a screening trial followed by SCS implantation based on the screening trial result or an SCS implantation-only strategy. Both groups will be followed-up for 6 months post randomisation. Duration for the main study protocol (i.e. start of recruitment to last patient recruited completing all study procedures) is expected to be 26 months. Patients’ participation within the trial will last for 6 months following implantation. The study design is summarised in Fig. 1.

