### Interventions

#### Screening trial and implantation strategy (usual care)

Patients randomised to this arm will receive a screening trial. A screening trial will consist of passage of either an external or internalised tunnelled SCS lead or leads attached to an external stimulator as per the centre’s routine practice. Those patients who have a successful screening trial will receive an implantable neurostimulation system while unsuccessful patients would not receive such an implant. Taking into consideration the RCTs included in the clinical evidence section of NICE TA159 [15], a successful screening trial will be defined as ≥ 50% pain relief and satisfactory on-table paraesthesia coverage (i.e. ≥ 80%) of the pain area, reduction in pain medications or improved quality of life and function, and successful location of leads at the anatomical target for paraesthesia-free therapies [10, 17]. Patients with an unsuccessful screening trial will not be implanted but all patients will continue follow-up to 6 months. Successful trial patients will go on to have the implantable pulse generator (IPG) implanted on a separate occasion.

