### Outcome measures

Patient outcomes will be collected at clinic visits at baseline (pre randomisation) and 6 months post randomisation unless otherwise stated.

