#### Primary outcome

The primary outcome measure is the comparison between pain NRS at 6 months between the screening trial and implantation strategy and the implantation-only strategy [19].

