#### Three-month and 6-month (end of study) visit following permanent implant

All patients will attend the clinic for the 3-month and 6-month appointments. Following the 6-month visit the patient will exit the study and be passed back to usual care within the pain clinic for ongoing management for the spinal cord stimulator.

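### Follow-up is timed from randomisation in some sections and from permanent implant in others, and the primary outcome names no origin; only randomisation is defined for every patient

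*Protocol article*

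**What the plan says.** All references are to the protocol article.

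**Timed from randomisation.** Study design: "Both groups will be followed-up for 6 months post randomisation". Outcome measures: "Patient outcomes will be collected at clinic visits at baseline (pre randomisation) and 6 months post randomisation unless otherwise stated".

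**Timed from implant.** Study design, later in the same paragraph: "participation within the trial will last for 6 months following implantation". The visit section is headed "Three-month and 6-month (end of study) visit following permanent implant", and its text says "All patients will attend the clinic for the 3-month and 6-month appointments".

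**No origin given.** The section that defines the primary endpoint reads: "The primary outcome measure is the comparison between pain NRS at 6 months between the screening trial and implantation strategy and the implantation-only strategy". For screening failures, the section on the screening trial and implantation strategy says "Patients with an unsuccessful screening trial will not be implanted but all patients will continue follow-up to 6 months".

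Three other statements bear on this. Data collection and visits collects all outcomes at the 3- and 6-month attendances. The Interventions and Implant visit sections place the permanent implant at a second, separate procedure in the screening arm and at a single procedure in the other arm. The implantation-only section makes the implant conditional on coverage and sensation, or on lead location, so that arm can also contain patients without an implant.

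**The concern.** An intention-to-treat comparison of two strategies needs one time origin that every randomised patient has. Randomisation meets that requirement. Permanent implant does not, for two reasons.

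First, patients who fail screening, and implantation-only patients who do not meet the on-table conditions, never acquire an implant date. A visit schedule counted from implant gives them no 3- or 6-month date.

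Second, implant comes after an extra procedure in one arm only. Counting from implant takes the wait for that procedure out of the comparison, although the wait is a consequence of the screening strategy. Time since randomisation at the outcome visit would then differ by arm.

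The primary NRS, the 30% and 50% responder proportions, the 6-month pain relief used as reference standard for sensitivity and specificity, and the QALY area under the curve all depend on when the 6-month visit takes place.

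**Working it through.** **1. The statements side by side.**

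| Section | Item timed | Origin |
|---|---|---|
| Study design, follow-up sentence | Follow-up, both groups | Randomisation |
| Study design, participation sentence | Participation | Implantation |
| Outcome measures | Outcome collection (default) | Randomisation |
| Primary outcome | Pain NRS at 6 months | Not stated |
| Screening trial strategy | Follow-up of screening failures | Not stated |
| 3- and 6-month visit heading | Visits at which outcomes are collected | Permanent implant |

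No section reconciles the two origins.

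**2. The plan's own sample size.** Inputs from Sample size determination: difference 2, SD 2.5, power 90%, alpha 5% (taken as two-sided), attrition 30%.
n per arm = 2 × (1.960 + 1.282)² × 2.5² / 2² = 32.8, so 33. Then 33 / 0.70 = 47.1, so 48. The t-test version gives 34, then 34 / 0.70 = 48.6, so 49. Both agree with the stated 50 to within two patients. The time origin does not enter this calculation.

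**3. Patients without an implant date in the screening arm.** The article does not predict its own pass rate, so the rates it cites in Background and Discussion are borrowed as an assumption. Number = 50 × (1 − pass rate).

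| Cited study | Pass rate | Of 50 without implant date |
|---|---|---|
| RCT against conventional medical management | 95% | 2.5 |
| High-frequency arm of the frequency RCT | 90/97 | 3.6 |
| Traditional arm of the frequency RCT | 81/92 | 6.0 |
| RCT against reoperation | 19/24 | 10.4 |
| Study with 75% success in the trial period | 75% | 12.5 |
| Prospective cohort of 55 | 34/55 (61.8%) | 19.1 |

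The number in the implantation-only arm cannot be estimated from the article.

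**4. Difference between arms.** The interval from randomisation to implant is not given for either arm. Let the screening arm's implant come w weeks later than the other arm's, and for simplicity take the other arm's implant as week 0. A visit at 26 weeks after randomisation then finds 26 − w weeks of device use in the screening arm; a visit at 26 weeks after implant falls at 26 + w weeks after randomisation.

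| Assumed w (weeks) | Device time at 26 weeks after randomisation | Weeks after randomisation if counted from implant |
|---|---|---|
| 2 | 24 | 28 |
| 4 | 22 | 30 |
| 8 | 18 | 34 |
| 12 | 14 | 38 |

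A common lag in both arms would shift both equally and leave the difference at w.

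**5. The stated duration.** Trial status gives recruitment as June 2017 to January 2019, in months only. From 30 June 2017 to 1 January 2019 is about 18 months; from 1 June 2017 to 31 January 2019 is 20 months. Adding 6 gives 24 to 26, against the 26 in Study design. That leaves 26 − 26 = 0 to 26 − 24 = 2 months for time to implant.

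**The case against.** The strongest reply is that the endpoint already has an origin. Outcome measures sets randomisation as the default, and the Primary outcome text beneath it says nothing different. The participation sentence concerns how long a patient stays in the trial, and the other implant reference is a heading. This has force: randomisation is the better reading. It does not remove the problem. The default carries the exception "6 months post randomisation unless otherwise stated", and the visit heading can be read as stating otherwise for the very attendances at which outcomes are collected. Study design contradicts itself in any case.

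A reader might infer that screening failures have no primary time point, or will be lost. The documents do not support that. The time point is undefined only if the implant clock governs, and the article says that all patients continue follow-up and attend the visits. What is missing is the date those visits count from. Even if all such patients were lost on top of 30% attrition, power for 2 points would fall from 91.7% (35 against 35) to between 91.0% (33.25 in the screening arm) and 83.3% (21.6). Selective loss would matter more than power.

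A reader might also infer that 26 months proves the randomisation clock. It is consistent with it, but an implant clock with a short lag also fits.

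On costs, the Economic evaluation refers to the study follow-up period, which Study design sets at 6 months after randomisation. Unequal cost and QALY windows would therefore arise only under the implant reading.

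Fig. 1 and Additional file 1 are not available here and may show how non-implanted patients are scheduled. They could show which clock was intended, but the conflicting sentences would remain.

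**Conclusion.** The article contradicts itself on the origin of its 3- and 6-month assessments, and the primary outcome text does not settle it. The contradiction rests on the wording alone.

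The consequences apply if sites schedule by the visit heading. The screening arm would then be seen later after randomisation; the direction follows from two procedures against one, and the size is unknown. Patients never implanted, in either arm, would have no visit origin. In the screening arm that is about 2.5 to 19 of 50 if the cited pass rates carry over. Those studies did not necessarily use this trial's composite definition of success, so the range shows scale and is not a forecast.

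The sample size stands. The point deserves correction because it concerns the timing of the primary outcome, and an analysis plan written later cannot recover an NRS collected at the wrong time.

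**What to change.** - In Primary outcome, state that the pain NRS is compared at 6 months post randomisation.
- In Study design, change the participation sentence to run from randomisation.
- Reword the 3- and 6-month visit heading so that these visits, and the outcomes, costs and QALYs taken from them, are timed from randomisation in both arms.
- State that patients not implanted, in either arm, attend at the same times.
- Record the implant date and describe time on SCS at the 6-month visit by arm.

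No separate visit at 6 months after implant is needed. For patients implanted late, it would fall after the 6-month visit at which they leave the study, and so would lengthen participation.

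The cost is a clarifying amendment and revised visit scheduling, with no extra patients. Recruitment was already under way when the article was written, so the actual time from randomisation should also be reported for visits already held. The downside is that screening-arm patients will have had less device time at the primary visit. That is part of the strategy effect and should be described as such.

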**Fig. 1 Fig1:**
[figure not shown]
Standard Protocol Items: Recommendations for Interventional Trials (SPIRIT) diagram. EQ-5D-5L five-level EuroQol-5D, PGIC Patients’ Global Impression of Change, SCS spinal cord stimulation

### Study population

One hundred adults (≥ 18 years) with chronic pain of neuropathic origin will be recruited from three centres: South Tees Hospitals NHS Foundation Trust (The James Cook University Hospital); Basildon and Thurrock University Hospitals NHS Foundation Trust; and Leeds Teaching Hospitals NHS Trust.

#### Inclusion criteria

Adults (≥ 18 years old) who are clinically considered to be candidates for SCS as per NICE TA159 [15].Pain of neuropathic nature of an intensity of at least 5 as assessed on a numerical rating scale (NRS).Patient has persistent pain for more than 6 months despite appropriate conventional medical and surgical management including transcutaneous electric nerve stimulation (TENS), acupuncture, oral analgesic agents, cognitive behavioural therapy as well as nerve blockade where appropriate.Satisfactory multidisciplinary assessment by a team with expertise in delivering SCS therapy.Patient capable of providing informed consent.

#### Exclusion criteria

Patient refusal to participate in the study.Presence of an ongoing pain condition considered by the investigator to overshadow the neuropathic pain condition to be treated with SCS.Current or previous treatment with an implanted pain relief device.Current participation or planned participation in other studies that may confound the results of this study.Ongoing anticoagulation therapy, which cannot be safely discontinued.Poor cognitive ability or lack of capacity.Unable to undergo study assessments or complete questionnaires independently.Patient is pregnant or planning to become pregnant during the course of the study.

#### Recruitment of patients

Patients will be recruited from the outpatient clinics of the three participating sites. Patients who are scheduled to have a spinal cord stimulator trial will be approached and given a Patient Information Sheet to take home to read. Informed consent will be obtained from suitable patients following a reasonable period of time by one of the Principal Investigators or delegated individuals at each site following International Conference on Harmonisation/Good Clinical Practice (ICH/GCP) guidelines [16].

### Interventions

#### Screening trial and implantation strategy (usual care)

Patients randomised to this arm will receive a screening trial. A screening trial will consist of passage of either an external or internalised tunnelled SCS lead or leads attached to an external stimulator as per the centre’s routine practice. Those patients who have a successful screening trial will receive an implantable neurostimulation system while unsuccessful patients would not receive such an implant. Taking into consideration the RCTs included in the clinical evidence section of NICE TA159 [15], a successful screening trial will be defined as ≥ 50% pain relief and satisfactory on-table paraesthesia coverage (i.e. ≥ 80%) of the pain area, reduction in pain medications or improved quality of life and function, and successful location of leads at the anatomical target for paraesthesia-free therapies [10, 17]. Patients with an unsuccessful screening trial will not be implanted but all patients will continue follow-up to 6 months. Successful trial patients will go on to have the implantable pulse generator (IPG) implanted on a separate occasion.

#### Implantation-only strategy

In the implantation-only strategy group, all patients with satisfactory on-table paraesthesia coverage (i.e. ≥ 80%) of the pain area and no dislike of sensations [18], and satisfactory anatomical lead location for paraesthesia-free devices, would receive a permanent implant in one surgery.

